**Methods for Objective 2:**

**Intervention package development**

The intervention package will be developed to change behavior of students, their parents and teachers. Therefore, the age group for measuring change in knowledge and practices will be 11-16 years for students & up to 65 years for parents & teachers.

Qualitative data will be collected by carrying 10 focused group discussions with students, their parents and teachers separately to understand their perception about risk factors and behaviors as well as about hypertension and diabetes.

**Phase 1 (Social assessment) –** Knowledge and practice assessment

**Phase 2-4 (Health sector assessment) -** Epidemiological, behavioral, environmental and motivational assessments.

**Phase 5-7 (Political assessment) –** Intervention, implementation & evaluation.

To develop a successful health promotion intervention for a community/population/group, it is important to know the demands and requirements of the people of the group. For health promotion planning there is need to widen the overlapped area between public perceived needs, actual needs and resources.

**Figure 1**: Health promotion planning model.

To achieve this, precede-proceed model will be followed and planning tool for health promotion intervention will be based on it.

**Phase 5 Phase 4 Phase 3 Phase 2 Phase 1**

Administrative and policy assessment Educational and ecological assessment Behavioral and environment assessment Epidemiological assessment Social assessment

Behavior and lifestyle

Predisposing factors

HEALTH PROMOTION

Quality of life

Health

Health education

Reinforcing factors

Environment

Enabling factors

Policy regulation organization

**Phase 6 Phase 7 Phase 8 Phase 9**

Implementation Process evaluation Impact evaluation Outcome evaluation

**Figure 2**: Precede-proceed model of Health Promotion.^87^

The social change approach will be applied. The first step will be to diagnose the various problems that affect the quality of life of the group and its members, their strengths and weaknesses, their resources and their willingness to change. This will be achieved by conducting various Focused Group Discussions (FGD’s) with the students.

Secondly, the epidemiological, behavioral, and environmental diagnosis will be done to know the physical and social actions that lead to the certain behavior and lifestyle and also the behavior of individuals (students) and actions of decision-makers that affect the behavior of the individuals at risk. This will help in framing more clear objectives and planning for intervention. This will be achieved with the help of questionnaires.

Then, the administrative and organizational concerns will be addressed prior to program implementation. After that intervention implementation, the process of the intervention implementation, its outcomes will be evaluated respectively.

**Intervention Implementation**

Awareness about the risky behaviors and will be created by group discussions during parents & teacher meeting to be held once in every three months. Following WHO Guidelines for Physical Activity and Diet will be followed while developing health promotion interventions among students.

WHO guidelines of physical activity for young people, aged 5-17 will be used for the intervention. Recommended levels of physical activity for adolescents are as follows.

For adolescents and young people, physical activity includes play, games, sports, transportation, chores, recreation, physical education, or planned exercise, in the context of family, school, and community activities.

In order to improve cardio-respiratory and muscular fitness, bone health, and cardiovascular and metabolic health biomarkers:

- Adolescents and youth should accumulate at least 60 minutes of moderate- to vigorous-intensity physical activity daily.
- Amounts of physical activity greater than 60 minutes provide additional health benefits.
- Most of the daily physical activity should be aerobic. Vigorous-intensity activities should be incorporated, including those that strengthen muscle and bone*, at least 3 times per week.

*For this age group, bone-loading activities can be performed as part of playing games, running, turning or jumping.

**Diet**

The exact make-up of a diversified, balanced and healthy diet will vary depending on individual needs (e.g. age, gender, lifestyle, degree of physical activity), cultural context, locally available foods and dietary customs. But basic principles of what constitute a healthy diet remain the same.

Diet evolves over time, being influenced by many factors and complex interactions. Income, food prices (which will affect the availability and affordability of healthy foods), individual preferences and beliefs, cultural traditions, as well as geographical, environmental, social and economic factors all interact in a complex manner to shape individual dietary patterns. Therefore, promoting a healthy food environment, including food systems which promote a diversified, balanced and healthy diet, requires involvement across multiple sectors and stakeholders, including government, and the public and private sector.

Intervention to the students in the schools will be given four times in a week with the help of champions, their buddies and the teachers of the selected schools.

***Intervention package for adolescents will include:***

1. Written information on the importance of different exercises and morning walk.
2. Students will be motivated for recommended level of salt and sugar consumption. Specific activities will be developed to motivate them.
3. Cheaper and healthier eating options available to them will be worked out in classroom settings.
4. Mid-day meal program will be checked for salt and sugar use. Teachers and meal providers will be guided for using recommended levels for salt and sugar.

***Intervention on parents & teachers***

1. Face to face interactions will be held two times during the period of intervention with the parents to brief and debrief them on what is being conveyed to students.
2. Information packages, such as, pamplets, spoons will be sent home through adolescents.
3. Facilitation for behavior change will be provided to parents when needed.
4. Class teachers will be involved in all the activities being carried out with students and parents.

**Detailed intervention plan:**

Physical activity sessions will be included with fun activities to keep students interested in the activity. Two students from each class (one monitor/ champion and one buddy) will be selected and trained for specific exercises. Exercises will be done for 45 minutes for 4 days in each week for 6 months. 45 minutes exercise schedule will consist of half an hour low intensity physical activity, such as, walking and stretching and another 15 minutes of vigorous exercises, such as cardio, consisting of brisk walking, running, and jumping jack and jumping ropes. Trained students, under the supervision of the teachers will lead the exercise classes.

| **Communication objectives** | **Audience** | **Barriers** | **Opportunities** | **Activities** | **Person responsible** | **Frequency & time in one cluster**  **(six month)** | **Channel of communication** |
| --- | --- | --- | --- | --- | --- | --- | --- |
| - To promote the recommended levels of salt, sugar, fruits and vegetable intake, and physical activity and reduction in the use of tobacco and alcohol - To manage hypertension and diabetes by discussing the importance of medicine adherence | Teachers: Teachers in direct interaction with randomly selected clusters (sections of 8^th^ grade) | Different class schedules of the teachers | School hours are the best time to interact with teachers in groups | Educational Sessions with teachers keeping communication objectives in focus | Researcher | Four sessions of thirty minutes during intervention period | Verbal (2-way communication) |
|  | Parents of adolescents from randomly selected clusters | Not all parents are available at the time of the parents-teachers meeting in schools | - Utilising home environment for promoting healthy diets by educating parents (as mostly, mothers are the food makers of the house) on the harmful effects of excessive intake of salt & sugar and less consumption of fruits and vegetables - The Parents Teacher Association (PTA) meetings may be used to interact with parents in school settings | Educational Sessions with parents keeping communication objectives in focus | Researcher | Four sessions of thirty minutes during intervention period | Verbal (2-way communication) |
|  | *Primary audience:* Adolescents of the randomly selected clusters (sections of 8^th^ grade)  *Secondary audience:* Parents & teachers of adolescents | - Vendors outside school premises - Unhealthy food options in the school canteens - Study load (tuitions after school hours & homework) - Stringent school time-table | - To catch adolescents before risky behaviours start developing - Using schools as a platform for promoting healthy behaviours | Educational classes and classroom discussions | Researcher | 30 minutes session every fortnight | Verbal (2-way communication) &  Digital audio-  visual method (PowerPoint presentation using the laptop) |
|  |  |  |  | Physical activity sessions | Researcher/ physical education teachers | Four sessions every week with each session of 30 minutes | Verbal (2-way communication) |
|  |  |  |  | Other interactive activities: Poster making competition & grow your own herbs | Researcher | Two sessions during intervention period with each session of about 45 minutes | Verbal (2-way communication) |
|  |  |  |  | Peer-to-peer education for reduction in the use of tobacco and alcohol | Researcher | One session every month with each session of 15 minutes | Verbal (2-way communication) |

**Behavior Change Communication Matrix- Intervention fr promoting recommended level of salt, sugar, fruits and vegetable intake along with increase in physical activity and reduction in use of tobacco and alcohol in public schools of Chandigarh**

Purpose of the Intervention: To promote positive changes in attitudes and behavior related to salt, sugar, fruits and vegetable intake, increase in physical activity and reduction in use of tobacco and alcohol among adolescents, their parents & teachers.

| **S.No** | **Risk Factors** | **Goal** | **Activities** |
| --- | --- | --- | --- |
|  | **Unbalanced dietary habits** | Recommended level of salt & sugar consumption  Recommended level of fruits and vegetable intake | Goal settings: ***Students***   - To learn how to measure the daily salt & sugar they are consuming in grams. - To remind everyone at home every day to consume less of salt & sugar. - To remove table salt - To stop the use of pickles and sauces - To stop junk food binging - To consume fresh seasonal fruits and vegetables daily   ***Parents***   - To measure the daily salt & sugar they are consuming and using for preparing food with the help of ***measuring tea spoons***.   ***Teachers***   - To measure the daily salt & sugar they are consuming and using for preparing food with the help of ***measuring tea spoons***. - To eat dinner two hours prior sleeping - To walk for 45-60 minutes daily - To take medicine regularly and get regular check-ups if hypertensive and diabetic and regular intake of folic acid tablets if anemic. - To make homemade sauces & pickles instead of consuming ready-made sauces and pickles. - To make fresh vegetables every day and consume fruits everyday |
|  | **Physical inactivity** |  | Goal settings:  ***Students***   - 45 minutes of less to moderate intensity exercise, at least 4 days a week   ***Parents***   - To walk for 45-60 minutes daily - To motivate children for outdoor activities   ***Teachers***   - To walk for 45-60 minutes daily - To motivate children for outdoor activities - To supervise physical activity classes efficiently |
|  | **Tobacco & alcohol use** | To create awareness about the ill effects of tobacco & alcohol | - Knowledge about the ill effects of tobacco & alcohol - To say no to tobacco & alcohol - To ask elders to not smoke or drink in front of you - Harmful effects of passive smoking - To help elders to reduce and stop smoking & drinking |

**Micro-planning of Intervention**

| **S.No** | **Focus of Intervention** | **Goal** | **Goal settings:** | **Activities** | **Time** | **Frequency in one cluster** |
| --- | --- | --- | --- | --- | --- | --- |
|  | **Unbalanced dietary habits** | To reduce salt & sugar consumption  To increase fruits and vegetable intake | ***Students***   - To learn how to measure the daily salt & sugar they are consuming in grams. - To remind everyone at home every day to consume less of salt & sugar. - To remove table salt - To stop the use of pickles and sauces - To stop junk food binging - To consume fresh seasonal fruits and vegetables daily   ***Parents***   - To measure the daily salt & sugar they are consuming and using for preparing food with the help of ***measuring tea spoons***.   ***Teachers***   - To measure the daily salt & sugar they are consuming and using for preparing food with the help of ***measuring tea spoons***. - To walk for 45-60 minutes daily - To take medicine regularly and get regular check-ups if hypertensive and   diabetic and regular intake of folic acid tablets if anemic.   - To make homemade sauces & pickles instead of consuming ready-made sauces and pickles. - To make fresh vegetables every day and consume fruits everyday | ***Students***   - Presentation - Activities - Discussions   ***Parents & teachers***   - Group discussions with parents and teachers | Approx. 30 minutes  30 minutes | One session every week  One session with parents and one with teachers in the duration of six months |

|  | **Physical inactivity** | To increase the level of physical activities and be more active | ***Students***   - 30 minutes of less to moderate intensity exercise, at least 4 days a week   ***Parents***   - To walk for 45-60 minutes daily - To promote outdoor activities among children   ***Teachers***   - To walk for 45-60 minutes daily - To promote outdoor activities among children - To supervise physical activity classes efficiently | ***Students***   - Physical education classes with the help of physical education teacher (any outdoor games like basketball, volleyball, cricket etc. as per the choice of the students)   ***Parents & teachers***   - Group meeting with parents and teachers | 30 minutes  30 minutes | 4 days/ week  One session with parents and one with teachers in the duration of six months |
| --- | --- | --- | --- | --- | --- | --- |
|  | **Tobacco & alcohol use** | To create awareness about the ill effects of tobacco & alcohol | - Knowledge about the ill effects of tobacco & alcohol - To say no to tobacco & alcohol - To ask elders to not smoke or drink in front of you - Harmful effects of passive smoking - To help elders to reduce and stop smoking & drinking | ***Students***   - Peer to peer education   ***Parents & teachers***   - Group meeting with parents and teachers for breaking various myths | 10-15 minutes  30 minutes | one session every month  One session with parents and one with teachers in the duration of six months |
|  | **Management of Hypertension and Diabetes** | To create awareness about methods to manage | - To help adults or anyone near them to manage these diseases - Behavioural modifications- Diet, physical activity, tobacco and alcohol use - Importance of medicine adherence | ***Students, parents and teachers***  ***Classroom discussion*** | 30 minutes | One session, separately with students, parents and teachers in the duration of six months |

**Methods for Objective 3:**

Effectiveness of the intervention will be measured using following indicators in the baseline and end line sample survey among adolescents:

Before the intervention, perceptions, knowledge and practice of case and control group adolescents will be assessed for the chronic diseases and their risk factors with the help of a questionnaire. This will help in measuring the extent of behavior change. This questionnaire will be used as one parameter to assess the effectiveness of the intervention as the same questionnaire will be used after the completion of the intervention. This will help in assessing the improvement of the perception, knowledge and practices.

For objective measurements, anthropometric measurements, such as, height and weight, along with physiological measurement (blood pressure), biochemical measurement (24-hour excretory sodium through spot urine samples) will be taken before and after intervention. This will be the second parameter to assess the effectiveness of the intervention. The net changes in primary and secondary outcome measures among parents and teachers will be considered as exploratory analysis,

| **Intervention** | **Impact** | |
| --- | --- | --- |
|  | **Direct** | **Indirect** |
| Diet | Participant | Family |
| Physical activity | Participant | Family |
| Alcohol | Participant | Family |
| Smoking | Participant | Family |

**Table:** Impact of different interventions on the participants and their families.

| **Expected outcome of Intervention** |
| --- |
| 1. Increase in knowledge about various chronic diseases and their risk factors 2. Positive response for behavior for diet and physical activity 3. Increase in normal BMI and waist-hip ratio 4. Reduction in risk factors of chronic diseases, such as, decrease in salt and sugar intake and increase in iron intake. 5. Reduction in the consumption of junk food. 6. Adherences to the medicine among those having chronic diseases. 7. Change in stage of behavior |

**Table:** Expected outcomes of intervention package

**Statistical Analysis**

Descriptive statistics such as mean, standard deviation, student’s t-test, will be done separately for both the sexes. Chi-square test will be done for categorical variables. Change in various indicators will be computed in intervention and controls. Multivariable regression will be done to measure the effect of intervention after controlling for the confounding variables, if any. All the statistical analysis will be done using Statistical Package for Social Sciences (SPSS) or R.

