**Study Design**

Study design is Cluster Randomized Controlled Trial. Each school will be one cluster.

Schools will be randomized to intervention and control group and net changes in the knowledge and practices related to chronic disease risk factors among students, their parents and teachers will be computed by measurements before starting the health promotion intervention and after implementation of the intervention in both intervention and control clusters.

Research approach will be mixed methods: It will have both qualitative & quantitative data. Quantitative data will be collected using validated tools. Qualitative data will be collected by carrying 10 focused group discussions with students, their parents and teachers separately to understand their perception about risk factors and lifestyle behaviors (2 with male teachers, 2 with female teachers, 2 with female students, 2 with male students and 2 with parents in government schools).

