**Sample size**

A total of 12 clusters were calculated based on the formula as shown below. Six clusters in intervention arm and six in control arm. As most of the schools in general have strength of 30 students in each section, the size of cluster (m) was taken to be 30 each from a randomly selected section of class 8^th^. Sample size for each indicator (risk factors: Unbalanced diet, physical inactivity, tobacco use and alcohol use) was calculated separately by using data from previous studies.

For quantitative data the sample size will be the same, i.e., 6 clusters in intervention arm & 6 in control arm for students, their parents & teachers in total. For qualitative data the sample size will be max up to 8 participants for each of the focus group discussion.

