**Formula used:**

**c = 1 + f [ π_0_(1 - π_0_)/m + π_1_(1 - π_1_)/m + k^2^ (π_0_^2^ + π_1_^2^) ] / (π_0_ - π_1_)^2^**

Where,

- c is the number of clusters per treatment arm
- f = 7.84 for 5% type I error and 80% power
- π_1_ is the expected proportion in the intervention arm
- π_0_ is the expected proportion in the control arm
- m is the number of individuals in each cluster (assumed equal in all clusters)
- k is the coefficient of variation in the (true) rates or proportions between clusters in each treatment arm

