**Sample size based on the risk factors**

| **Risk Factor** | ***π_0_*** | ***π_1_*** | ***K*** | ***C*** |
| --- | --- | --- | --- | --- |
| Inadequate fruits and vegetable intake^82^ | 0.852 | 0.596 | 0.025 | 12.2 |
| Excess salt intake^83^ | 0.223 | 0.162 | 0.094 | 12.1 |
| Sugar intake (g/day)^84^ | 0.507 | 0.355 | 0.041 | 12.5 |
| Physical inactivity^85^ | 0.232 | 0.162 | 0.099 | 12.1 |
| Tobacco use^85^ | 0.049 | 0.034 | 0.163 | 11.4 |
| Alcohol use^86^ | 0.345 | 0.242 | 0.057 | 12.4 |
| Total clusters selected: Twelve | | | | |

Schools will be selected randomly for control and intervention groups (based on the consent) from the list of randomly selected schools.

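### Schools are randomised, but the t-tests, chi-square tests and regression named for the analysis make no allowance for clustering, so between-arm standard errors are too small if pupils within a school are at all alike

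*Protocol*

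**What the plan says.** Protocol, Study Design: "Study design is Cluster Randomized Controlled Trial. Each school will be one cluster". Protocol, Sample size: "Six clusters in intervention arm and six in control arm", and "the size of cluster (m) was taken to be 30 each", drawn from one randomly chosen 8th-grade section per school.

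The sizing recognises that schools differ. In the formula, "k is the coefficient of variation in the (true) rates or proportions between clusters in each treatment arm", and the table of risk factors gives a value of k for each of six outcomes.

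The Statistical Analysis section is one short paragraph. It lists Student's t-test among the descriptive statistics, to be run separately by sex. It then says "Chi-square test will be done for categorical variables" and that changes will be computed in each arm. For the effect itself it says "Multivariable regression will be done to measure the effect of intervention after controlling for the confounding variables, if any". Neither this section nor any other part of the protocol mentions a random effect for school, generalised estimating equations, a cluster-robust variance, a school-level summary or a small-sample correction.

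**The concern.** The unit of randomisation is the school, so the evidence on the intervention comes from six schools against six. Pupils in a study section share a classroom, teachers, exercise sessions and, where one is provided, a mid-day meal whose salt and sugar content the intervention itself addresses. Some similarity within schools is to be expected on the hypothesis outcomes (salt, sugar, fruit, vegetables, inactivity, tobacco and alcohol).

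A t-test, chi-square test or regression that treats pupils as independent leaves that similarity out of the standard error. Intervals come out too narrow, and a nominal 5% test rejects a true null more often than 5% of the time. This would affect every between-arm comparison. The protocol allows for clustering when it sets the number of schools and then names an analysis that does not.

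**Working it through.** **Inputs from the protocol.** Six schools per arm and m = 30, so 12 × 30 = 360 pupils. The formula states "f = 7.84 for 5% type I error and 80% power"; 7.84 = (1.96 + 0.84)², which corresponds to a two-sided 5% level. Control proportions π0 and coefficients of variation k come from the table of risk factors. For example, the fruit and vegetable row reads "0.852 | 0.596 | 0.025 | 12.2" for π0, π1, k and c.

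The table's c column is not used here. At m = 30 the printed formula gives 2.5 to 96.6 clusters per arm across the six outcomes, against the 11.4 to 12.5 printed. That is a separate matter and this point does not depend on it.

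**Step 1: the ICC implied by the protocol's k.** Under the null both arms have proportion π0. The between-school variance is (kπ0)² and the total variance is π0(1 − π0), so ICC = k²π0/(1 − π0). For fruit and vegetables: 0.025² × 0.852/0.148 = 0.0036.

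**Step 2: true type I error of a nominal 5% test that ignores schools.** The design effect is DE = 1 + (m − 1) × ICC, and the true error is 2 × [1 − Φ(1.96/√DE)]. For fruit and vegetables: DE = 1 + 29 × 0.0036 = 1.104, 1.96/√1.104 = 1.865, and the error is 6.2%.

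| Outcome | π0 | k | ICC | DE (m = 30) | Type I error |
|---|---|---|---|---|---|
| Fruit and vegetables | 0.852 | 0.025 | 0.0036 | 1.104 | 6.2% |
| Salt | 0.223 | 0.094 | 0.0025 | 1.074 | 5.9% |
| Sugar | 0.507 | 0.041 | 0.0017 | 1.050 | 5.6% |
| Physical inactivity | 0.232 | 0.099 | 0.0030 | 1.086 | 6.0% |
| Tobacco | 0.049 | 0.163 | 0.0014 | 1.040 | 5.5% |
| Alcohol | 0.345 | 0.057 | 0.0017 | 1.050 | 5.6% |

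**Step 3: sensitivity to the ICC.** The protocol gives no ICC, so the values below are assumptions. The t-tests are to be run by sex. With an even split (also an assumption) there are about 15 pupils per school in each test, and DE = 1 + 14 × ICC.

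| Assumed ICC | DE, m = 30 | SE too small by a factor of | Type I error, pooled | DE, m = 15 | Type I error, by sex |
|---|---|---|---|---|---|
| 0.01 | 1.29 | 1.14 | 8.4% | 1.14 | 6.6% |
| 0.02 | 1.58 | 1.26 | 11.9% | 1.28 | 8.3% |
| 0.05 | 2.45 | 1.57 | 21.0% | 1.70 | 13.3% |
| 0.10 | 3.90 | 1.97 | 32.1% | 2.40 | 20.6% |

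At the protocol's own k, the by-sex error is 5.2% to 5.6%.

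**Step 4: simulation check.** 20,000 null trials were simulated per ICC, with six against six schools of 30 pupils and a continuous outcome. The pupil-level t-test rejected in 4.9% of trials at ICC 0, then 8.4%, 12.0%, 21.4% and 32.2% at the four assumed ICCs, which agrees with the closed form. A t-test on the 12 school means (12 − 2 = 10 df, critical value 2.23) stayed between 4.8% and 5.3% throughout.

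**Step 5: how tight the protocol's k is.** The between-school standard deviation is kπ0. For five of the six outcomes it lies between 0.020 and 0.023, so true school prevalences are taken to differ with a standard deviation of about 2 percentage points. The protocol gives no basis for these values. For alcohol, a standard deviation of about 7 points gives ICC = 0.07²/(0.345 × 0.655) = 0.02, and a type I error of about 12% for a pooled test.

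**The case against.** The best reply is that the protocol never calls these tests individual-level. The t-test sits among descriptive statistics, the chi-square sentence does not say that it compares arms, and the term multivariable regression does not exclude a mixed model or generalised estimating equations. The software named can fit both, and a statistical analysis plan that is not shown may add the school term. This stands to the extent that the protocol does not rule out a clustered regression, and a reader who infers that it commits to ordinary regression goes beyond the text. It does not remove the point. The section is not silent: it names specific methods for a cluster-randomised trial, their standard forms assume independence, and it refers to no later plan. Followed as written, it gives the wrong standard errors.

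Three further limits stand:

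- A reader might infer that all these tests use about 358 degrees of freedom (360 − 2). That is not so. A chi-square test on a 2×2 table has 1 df, the by-sex t-tests have roughly half of 358, and regression loses more to covariates.
- The m = 30 figures describe pooled tests and overstate the inflation of the by-sex t-tests.
- The calculation is for a single end-line comparison, whereas the protocol plans net changes from baseline. The ICC of a change is not given and may be lower or higher.

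**Conclusion.** The point holds: the stated analysis does not match the randomisation, and the direction of the error is certain for any positive ICC.

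Its size is less certain. On the only between-school figures in the protocol, a pooled nominal 5% test has a true error of 5.5% to 6.2%, which is a modest excess. It reaches about 8%, 12%, 21% or 32% only at assumed ICCs of 0.01, 0.02, 0.05 or 0.10, and about 7%, 8%, 13% or 21% for by-sex tests under an even split. A reader might infer that false-positive rates of 20% to 30% are to be expected, or that a positive result would merely reflect differences between schools. The documents do not support either reading, because they give no ICC of that size.

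The correction is still needed. The validity of every between-arm test should not depend on unexplained k values that put most school standard deviations near 2 percentage points.

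**What to change.** Amend all three sentences in the Statistical Analysis section. Changing the chi-square sentence alone would leave the regression that estimates the effect as it is. Suggested text:

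*Every between-arm comparison will be made on the 12 school-level summaries (the mean or proportion in each school), using the change from baseline, by a two-sample t-test with 10 degrees of freedom. Individual-level t-tests and chi-square tests will be used for description only.*

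An equally acceptable primary method is a regression of the school's end-line value on arm and its baseline value, which leaves 12 − 3 = 9 df. One of the two should be named before outcome data are seen, so that the choice cannot follow the results. For by-sex comparisons, each school's summary is taken over pupils of that sex.

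A mixed model with a random intercept for school may be a stated secondary analysis, with small-sample degrees of freedom (Satterthwaite or Kenward-Roger) for continuous outcomes. Those corrections belong to linear mixed models, which is one reason to keep the school-level analysis primary for binary outcomes. Tobacco use is a clear case: at π0 = 0.049 a school of 30 is expected to have about 1.5 users (30 × 0.049).

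The change is to wording only, needs no new data, and runs in the software already named. Intervals become wider and correct. The critical value alone widens them by 2.23/1.96 = 1.14. With the standard-error factor √DE at the protocol's own k (1.02 to 1.05), the total is about 1.16 to 1.20. Nominal power falls accordingly and should be restated.
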